### Blinding

The randomization service will generate a unique trial identification number for that participant, which will be used on Case Report Forms. Research assistants will be blind to allocation status of participants, but the participants and those providing clinical care will not. Researchers will be asked to keep a contemporaneous record of any instances in which treatment allocation is disclosed to them. When a researcher is unblinded, we will arrange for a second researcher who is blinded to complete the six-month follow-up assessment.

### Study logistics

#### Recruitment

Potential participants will initially be approached about the study by any healthcare professional who is involved in their care. If staff have a patient under their care who they believe meets the eligibility criteria for the study, they will introduce the patient to the study at an appropriate time by briefly describing it to them. The patient must provide verbal agreement to discuss their eligibility and possible enrolment into the trial with a member of the research team before any further study process can take place. If a patient gives verbal agreement, a researcher will phone them to explain the study in greater detail. The researcher will then post or email a copy of the patient information sheet. Potential participants will be given no less than 24 h from receiving the information sheet to consider the information and the opportunity to question the researcher or other independent parties about their participation in the trial. Researchers will then arrange to meet potential participants to obtain written informed consent. A copy of the signed Informed Consent form(s) will be given to the patient. The original signed form(s) will be retained at the trial site. We will aim to recruit the study sample of an eight-month period.

#### Screening, baseline, and follow-up interviews

If consent is given and documented, a Screening Assessment Case Report Form will be completed with the participant. If the participant fulfils the eligibility criteria, they will then complete the Baseline Assessment and be randomized (see Fig. 2). Following randomization, the participant’s GP and referring clinician will be informed of their enrolment into the trial.

**Fig. 2 Fig2:**
[figure not shown]
Study *flow chart*

Study participants will be contacted at three months by a study researcher to confirm contact details and as a reminder about the six-month assessment. A follow-up interview will then be scheduled for six months after randomization. All participants will be offered a £20 honorarium following completion of the six-month follow-up interview.

#### Adverse events

All adverse events (AEs) will be recorded from the time a participant gives consent until 30 days after participation. In keeping with EU guidance on the collection and verification of AE reporting in clinical trials, serious adverse events (SAE; i.e. those that result in death, are life-threatening, require hospitalization or prolongation of existing inpatients’ hospitalization, or result in persistent or significant disability or incapacity) and non-SAEs will be recorded on event forms, detailing as much of the event as possible to be reviewed and signed by Principal Investigator [44]. The Principal Investigator will assess: (1) the seriousness of the event; (2) the likelihood of causality to the event; and (3) the severity of the event. The Researcher will ask participants during any contact or scheduled visit about AEs.

The study may be subject to inspection and audit by Central and North West London NHS Foundation Trust under their remit as sponsor and other regulatory bodies to ensure adherence to GCP and the NHS Research Governance Framework for Health and Social Care.

### Data management and analysis

Data will be entered into a password-protected Microsoft Excel spreadsheet/database held on a secure server. Study data will be archived securely and then safely destroyed after 15 years. Analysis and reporting of the trial will be in accordance with CONSORT guidelines.

Data analysis will focus principally on descriptive data on recruitment rates, characteristics of participants, attrition from the trial, non-adherence to therapy, and follow-up. The effect of treatment on outcomes will be estimated on an intention-to-treat basis using differences in scores on study outcomes and confidence intervals. We will explore the distribution of the outcomes to investigate assumptions of normality in order to plan the analysis and sample size for the definitive trial. We will also analyze the cost of the intervention using data from the proformas completed by those delivering PSP. We will also estimate costs of TAU that participants receive using data from the Adult Service Use Schedule. These data will allow us to identify the main cost components which would need to be captured in a subsequent phase, full-scale trial.

Contemporaneous notes will be made during each interview and uploaded to NVivo analytical software before thematic analysis [45]. To generate an initial coding framework, an independent thematic analysis will be conducted on a sample of transcripts and a session held to discuss and refine the thematic structure. This initial coding frame may be further refined as the analysis progresses in response to emergent themes. Supported by NVivo, the coding framework will be applied to the data (indexing) with the aim of allocating all data to a theme. Where new codes are identified, previously coded transcripts will be re-checked to ensure that extracts of data are coded consistently throughout. Full copies of notes will be retained to ensure context is maintained. The aim of the analysis will be to describe the range of experiences and responses to the intervention, highlighting any patterns and divergences in respondent accounts which support the key research questions relating to feasibility, acceptability, and optimization of both the intervention and trial design.

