#### Baseline: eligibility and covariates

At baseline, we will collect demographic details and assess eligibility using the Standardized Assessment of Severity of Personality Disorder (SASPD) [32]. A score ≥ 8 on the SASPD provides a reliable assessment of the likelihood of personality disorder according to ICD-11 criteria [32]. Those who score < 8 on the SASPD will not be eligible to take part in the study. Those who are ineligible will be thanked for their time and informed of the reason(s) for this. We will also ask participants to complete the International Personality Disorder Examination (IPDE) Screening Questionnaire, a 77-item self-complete questionnaire, which provides a reliable indication of specific personality disorders using DSM-IV criteria [33]. We will use data from the IPDE to describe the range of personality problems experienced by people who take part in the study.

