#### Follow-up assessments

All study participants will complete a six-month follow-up assessment. At the six-month follow-up, the researcher will ensure that all the study outcomes that were assessed at baseline are reassessed, i.e. the Work and Social Adjustment Scale, the Warwick and Edinburgh Well-Being Schedules, suicidal thoughts and behavior using items from the National Household Survey of Psychiatric Morbidity, the EQ-5D-5 L, the Client Satisfaction Questionnaire, the Adult Service Use Schedule, patient-rated Clinical Global Impression and the five-point Likert scale on how confident they are in their ability to manage crises.

In addition to this, we will seek additional consent from study participants to take part in a qualitative interview. Following completion of the six-month follow-up interview, up to 20 participants will be invited to take part in a separate interview with a researcher with lived experience of using mental health services. During this interview, participants will be asked about their experience of taking part in the study and any steps they think we could take to improve the design of a future definitive trial. The interview will be semi-structured and guided by a topic list which will be applied flexibly. The sample for this qualitative component of the study will be purposively selected to ensure that men and women of different ages and ethnicities are selected from those in both the active and control arm of the trial. Participants from the active arm of the trial will also be selected to ensure that both those who engage and drop out of PSP are included.

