### Assignment of interventions

After consenting to participation and completing screening assessments, people who are found to be eligible will be randomly allocated to PSP or TAU by a clinical trial manager at the Centre for Psychiatry, Imperial College London. A randomization list will be generated using the independent web-based service “sealed envelope” (https://www.sealedenvelope.com/simple-randomiser/v1/lists). Equal numbers of participants will be randomized to the two arms of the trial and stratification will occur by gender and study center. Throughout the study, the randomization list will be encrypted and held with the Trial Coordinating Office in order to keep the study researchers blind against treatment allocation. At the end of the study the randomization list will be unencrypted and placed in the Trial Master File. Equal numbers of participants will be randomized to each arm of the trial. Randomization will be stratified according to the referring team and gender of the participant.

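### The stated effect estimator names no baseline adjustment although every outcome is measured at baseline; a baseline-adjusted difference would usually be more precise, at no extra data cost

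*Protocol article*

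**What the plan says.** One sentence, in Data management and analysis, fixes how effects are estimated: "The effect of treatment on outcomes will be estimated on an intention-to-treat basis using differences in scores on study outcomes and confidence intervals". It follows a statement of priorities: "Data analysis will focus principally on descriptive data on recruitment rates, characteristics of participants, attrition from the trial, non-adherence to therapy, and follow-up". The next sentence gives the planning use of the outcome data, and reads in part: "We will explore the distribution of the outcomes to investigate assumptions of normality in order to plan the analysis and sample size for the definitive".

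Baseline: study outcomes lists the measures taken at entry. Follow-up assessments then requires that at six months "all the study outcomes that were assessed at baseline are reassessed". One baseline section is headed "Baseline: eligibility and covariates", but no analysis model is attached to it.

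Assignment of interventions describes the strata twice. First, "stratification will occur by gender and study center"; later in the same paragraph, "Randomization will be stratified according to the referring team and gender of the participant". The abstract agrees with the second.

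**The concern.** Most outcomes have a paired baseline score, and the allocation is stratified. The stated estimator mentions neither. The two readings closest to its wording are a between-arm difference in six-month scores and a between-arm difference in change from baseline. The first makes no use of the baseline score. The second uses it, but with a fixed weight of one, which is too much when the correlation is low. A regression on baseline lets the data choose the weight.

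Two things are at stake. One is the precision of effect estimates based on some 45 to 60 people. The other is that an open wording lets the choice among follow-up, change and adjusted differences be made after the results are seen. If the stratification factors are prognostic, an unadjusted interval is also somewhat conservative, because it takes no credit for the balance that stratification produced.

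**Working it through.** **Inputs from the protocol article.** The target is 60 participants with equal allocation (Sample size; Assignment of interventions). Follow-up completion of 75% is a progression criterion, so 0.75 × 60 = 45. The article gives no SD, interval width or correlation, so it has no precision figure of its own to reproduce. Its one related figure checks: 0.80 × 60 = 48.

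**Assumptions.** The baseline to follow-up correlation r is not in the documents; 0 to 0.7 is shown. Baseline and follow-up variances are taken as equal. Half-widths are in units of the outcome SD, for N analysed and 1:1 allocation.

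**Formulas for the 95% half-width.**

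- Follow-up difference: t(0.975, N−2) × √(4/N). For N = 45: 2.017 × 0.298 = 0.601.
- Change-score difference: the same × √(2(1−r)).
- ANCOVA on baseline: t(0.975, N−3) × √(4/N) × √(1−r²) × √(1 + 1/(N−5)). The last factor is the expected cost of fitting the covariate. For N = 45 and r = 0.5: 2.018 × 0.298 × 0.866 × 1.012 = 0.528.
- ANCOVA plus five stratum terms that are not prognostic (six covariates in all): t(0.975, N−8) × √(4/N) × √(1−r²) × √(1 + 6/(N−10)). Five is an assumed count, since the number of teams is not given.

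**Results for N = 45.**

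| r | Follow-up | Change score | ANCOVA on baseline | ANCOVA + 5 non-prognostic terms |
|---|---|---|---|---|
| 0 | 0.601 | 0.850 | 0.609 | 0.654 |
| 0.3 | 0.601 | 0.711 | 0.581 | 0.624 |
| 0.5 | 0.601 | 0.601 | 0.528 | 0.566 |
| 0.7 | 0.601 | 0.466 | 0.435 | 0.467 |

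Against the follow-up difference, ANCOVA on baseline is about 1% wider at r = 0 and 3%, 12% and 28% narrower at r = 0.3, 0.5 and 0.7. With all 60 followed up, the follow-up difference gives 0.517, and ANCOVA gives 0.522, 0.498, 0.452 and 0.373.

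**Change scores against ANCOVA.** Apart from the small fitting cost, the relative variances are 2(1−r) and 1−r². Their difference is (1−r)², which is never negative. The change score is therefore no more efficient than ANCOVA at any r, and it is worse than the plain follow-up difference when r is below 0.5.

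**Stratum terms.** Adding five that are not prognostic makes the interval about 4% wider than the unadjusted one at r = 0.3. At r = 0.5 it cuts the gain from 12% to 6%. The firm gain comes from the baseline score; team terms have to be added sparingly.

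**The case against.** The best defence is that the sentence does not say unadjusted. An adjusted mean difference is also a difference in scores, one heading mentions covariates, and a journal article commonly leaves the model to a statistical analysis plan that is not shown. This stands to the extent that nobody can say the trial has decided to discard its baseline data. A reader might infer that from the sentence, but the wording is open and does not support it. The sentence does, however, state an estimator, and its two most natural readings are both improved by baseline adjustment.

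A reader might also infer that the trial will hand the wrong SD to the definitive trial, so that the latter would be oversized by a factor of 1/(1−r²). The documents do not support this. No planning SD is fixed, the definitive analysis is left open, and the marginal SD is a legitimate planning quantity. Because both measurements are collected, the correlation can be computed at any time.

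Three further points stand and limit the weight of the concern:

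- The gain depends on an unknown correlation and vanishes near zero.
- Nothing in the article shows that gender or team is prognostic, and several team terms could cost precision.
- Chance baseline imbalance does not bias an unadjusted randomized comparison; its variability is already in the interval.

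**Conclusion.** The point holds as a modest, free improvement. The only stated estimator names no baseline or stratification adjustment. Read as a follow-up or change-score difference, it gives up precision that the design already makes available. With 45 followed up, the half-width is about 0.60 SD unadjusted, against about 0.58, 0.53 and 0.44 SD with ANCOVA at assumed correlations of 0.3, 0.5 and 0.7. At zero correlation there is essentially nothing to gain (0.61 SD).

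The consequence is limited. The analysis is principally descriptive, the sample size does not rest on power, and the three numerical progression criteria concern recruitment, uptake and follow-up. None depends on an effect estimate or its interval.

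The two descriptions of the strata must be reconciled before any stratum term can be specified. Sample size speaks of a single center, so a model built on center could have no center term at all, while one built on referring team could have several.

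**What to change.** Replace the estimator sentence with wording such as:

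> Effects will be estimated by intention to treat. For continuous outcomes measured at baseline, the between-arm difference at six months will be estimated by linear regression of the six-month score on arm, baseline score and gender, with a 95% confidence interval. The correlation between baseline and six-month scores will be reported with the outcome SD.

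Reconcile the two statements of the stratification factors in Assignment of interventions. If referring team is confirmed, include it only as a random intercept or with small teams pooled. Leave the Clinical Global Impression item without its own baseline as a covariate, because it is itself a rating of change.

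The cost is a few lines of text and no new data. Statistically it is a few degrees of freedom, with a slight loss of precision if the added stratum terms turn out not to be prognostic. The wording should be settled before outcomes are compared by arm.

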### Progression criteria

Our criteria for determining the success of the feasibility study are: recruitment of at least 48 participants (80% of the target study sample of 60 participants); uptake of the low intensity intervention by at least 60% of participants in the active arm of the trial; and completion of follow-up interviews at six months by 75% of study participants. To determine the feasibility of calculating a cost analysis of health economics, we will record completion rates for the cost data and analyze them to determine what the main cost-drivers are likely to be in a full clinical trial.

### Ethics

Approval for the research has been given by the South Central Research Ethics Committee (Ref: 16/SW/0255) and from the Research and Development departments of the participating NHS Trust. We will ensure that the trial is conducted in full conformity with the current revision of the Declaration of Helsinki (last amended 13/09/2017. Version 4.0) and with the Medicines for Human Use (Clinical Trials) Regulation 2004 transposed into law from the EU Clinical Trials Directive 2001/20/EC, the EU Good Clinical Practice Directive 2005, and all current and future acts and requirements pertaining to its conduct.

Each study participant will be assigned a unique trial identification number at the start of the assessment process. This number will be written on all clinical assessment forms/datasheets and databases used to record data on study participants. A hard copy of a record sheet linking patient identity, contact details, and trial identification number for all participants will be kept at each site. It will be placed in the Investigator Site File, in a locked filing cabinet, separate from the paper Case Report Forms and other documents relating to a participant, which will be anonymized. Recorded data will be entered onto an electronic data management system that will use the trial identification number rather than the participant’s name or other information that could identify them.

## Discussion

This trial aims to generate data to test the feasibility of using a randomized trial to examine the effects of a low intensity intervention for people with personality disorders. Current guidance from the National Institute for Health and Care Excellence caution against the use of brief interventions for people with borderline personality disorder [4]. Despite this guidance, mental health services are under increasing pressure to try to ensure that more people with personality disorders receive evidence-based interventions and treatments. PSP is a new approach aimed at helping people with personality disorders, which is delivered to individuals rather than to groups of people, and is based on principles derived from longer-term interventions for people with personality disorders and recommendations of an expert panel of service users and providers.

PSP is a person-centered intervention which allows therapists and patients to develop an agreed plan for providing short-term psychoeducation and support that focuses on what matters most to the patient. Rather than attempting to treat the person’s personality, PSP aims to provide people with information about the nature of personality-related problems and psychological approaches derived from longer-term psychological treatments that may help people improve their mental health.

This trial has a number of strengths and limitations. It is designed to be pragmatic with broad inclusion criteria, limited exclusion criteria, and relatively short outcome assessment.

By enabling people with substance misuse problems, including substance dependence, to take part in the study we will be testing an intervention for an important group of people with personality disorders who are often excluded from existing interventions for people with this condition [46]. Unlike most trials of interventions for people with personality disorders, we will not make entry into the study dependent on a potential participant meeting validated criteria for the condition. Instead potential participants will need to meet criteria for “probable” personality disorders using the SASPD. We have decided not to include a more formal examination of personality disorders, because validated semi-structured instruments designed to make these assessments are lengthy (often taking > 1 h to complete). Furthermore, in a previous trial of problem-solving therapy for people with personality disorders in a secondary care setting, we found that nearly all those referred to the trial (650/682, 95.3%) met the criteria for personality disorders; those that did not still had significant personality pathology [47].

The trial combines the collection of both qualitative and quantitative data in order to make a comprehensive assessment of the acceptability and feasibility of the study design and in an effort to generate data that could help inform the design of a larger future explanatory trial.

We will be assessing the feasibility and acceptability of a range of outcomes. These are based on recommendations of both users and providers of services for people with personality disorders [48]. By including the patient version of the CGI Scale in the follow-up interview we will be able to examine whether the two treatment conditions are associated with negative as well as positive changes for participants. This information, together with the qualitative data we will be collecting, will enable us to examine concerns about possible negative effects of short-term interventions for people with personality disorders [4, 47].

Limitations of the trial include the absence of detailed information about the “type” of personality disorders which patients experience and the relatively short follow-up period. Our use of the SASPD will ensure that we will have reliable information about the severity of the personality disorders of study participants but will not enable us to describe the proportion of people who meet criteria for borderline, antisocial, and other specific personality disorders [32]. While this will limit our ability to compare the results of the trial with results of previous trials of borderline personality disorder, we have purposefully adopted an approach to the diagnosis of personality disorders that will form the basis of revised World Health Organization criteria which are primarily based on severity of interpersonal functioning and sense of self rather than type of personality-related problems [49].

We decided to restrict the length of follow-up in the study to six months because our primary aim was to establish the rate of recruitment in the trial as well as the acceptability and uptake of the intervention we are testing. However, personality disorders are long-term conditions and a future larger-scale explanatory trial would benefit from having a longer-term follow-up of 12–18 months.

This trial faces a number of challenges which will need to be overcome if we are to recruit to target. In addition to pressures of workload and other factors that may deter clinicians from referring people to clinical trials, staff may be concerned about the impact of their patient being randomized to “treatment as usual,” which many consider unsatisfactory. Clinical staff may prefer the option of referring patients for assessment for psychological treatment from a psychologist or psychotherapist. However, such services typically have long waiting lists and referral criteria which exclude some of the patients we aim to recruit to this study (such as those judged at risk of severe self-harm and those with coexisting substance misuse). Potential participants may also be unhappy about the prospect of being randomly allocated to the two arms of the trial and may have a preference either for continuing to receive care from their existing team or for receiving the new intervention that we are testing. For this reason, we have designed patient information sheets to reflect the similarities as well as the differences between the two treatment conditions in the trial. For instance, both treatment conditions aim to work with people in the short to medium term with a view to discharging the patient from secondary care mental health services. Participants in both arms of the trial will also have access to other secondary care services including crisis helplines, review of medication, and referral to longer-term psychological therapies if these are indicated. We will be examining the views of study participants on this and other aspects of the trial design as part of the process evaluation we are conducting in parallel to the randomized trial.

